##### Analysis of secondary outcomes

Analyses of secondary outcomes will follow a broadly similar strategy. These will include the data at 6-month follow-up from the other outcomes (SNOT-22 subscales, NOSE, DOASS, SF-36) and that for all outcomes at 12-month follow-up.

Subjective scales, tabulated by arm and overall at randomisation, 6-month and 12-month follow-ups, will be compared by both summary statistics and graphical representation. Multiple regression will be used to investigate longitudinal outcome scores between treatment groups at follow-up time points. Variation between participants will be included as a random effect with an assumed normal distribution. Analysis will include the stratification factors of baseline severity and gender. Further adjusted analyses will include terms for baseline values of the scores and key demographic and clinical covariates.

Adverse events will be tabulated according to World Health Organisation (WHO) Common Terminology Criteria for Adverse Events (CTCAE) grade version 4.03. Number of severe (CTC grade 3, 4 or 5) will be reported as a proportion of all AEs. Number of participants experiencing at least one severe CTCAE will be reported as a proportion of all participants. Surgical complication/failure and re-intervention will be tabulated and will not subject to statistical testing. Technical failures from operations where widening of nasal airway was achieved yet the symptoms persist will be reported.

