On the sidewalls of the nose are ‘turbinates’, tissue structures which are rich in blood vessels and glands. Often when the septum narrows one side of the nose, it creates a larger space on the other side, into which the turbinate on that side expands. Medical management using topical nasal steroid sprays decongests the nasal lining and may lead to improvement in the symptoms of nasal blockage. However, such treatments are required on a daily, ongoing basis and in practice may not be successful. In addition, side effects of nasal dryness, irritation and bleeding may impact on treatment satisfaction and compliance. When surgery to straighten the septum is carried out, some surgeons also reduce the contralateral turbinate tissue. Potential complications of septoplasty include septal perforation, septal adhesions and bleeding [4]. Post-operative pain is common although this is reduced if sutures rather than nasal packing are used [4–6]. Patients typically are advised to take several days off work or usual activities after the operation. Septoplasty has no defined selection criteria, particularly in patients whose principal symptoms are sleep related, and clinical practice varies in different centres. The mode of action of septoplasty in sleep-related breathing disorders is not fully understood [7–9].

The effectiveness of septoplasty with or without turbinate surgery remains unclear and there is a lack of high-quality evidence of its benefit in the literature [10, 11]. Not all patients improve with surgery. Estimates of persistent septal deviation following a septoplasty procedure range from less than 6% [12] to 20% [13]. Where septoplasty fails and further surgery becomes necessary, revision rates are reported to be high [14]. There is also a lack of robust evidence about the additional benefit of turbinate surgery [11]. One study showed reduced revision rates for septoplasty when the turbinate tissue is reduced [15]; other studies report no added long-term benefit from turbinate reduction [16–18].

Currently, most septal surgery is based on subjective, unstandardised clinical impressions of the contribution of the nasal septum to patients’ symptoms. There is also no good comparative evidence regarding alternatives to septal surgery; nor about who might most benefit, to inform patients’ and doctors’ shared surgical decision-making [11].

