##### Safety outcomes

Safety outcomes will be measured by the number and characteristics of any AEs, and surgical complication/failure and re-intervention within 12 months.

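### Severe adverse events as a share of all adverse events is not a measure of risk and can mislead if read by arm; the stated participant-level proportion covers grade 3–5 only

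*Protocol article*

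**What the plan says.** The section on analysis of secondary outcomes in the protocol article gives these safety summaries:

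- a tabulation by grade: "Adverse events will be tabulated according to World Health Organisation (WHO) Common Terminology Criteria for Adverse Events (CTCAE) grade version 4.03";
- an event-level ratio: "Number of severe (CTC grade 3, 4 or 5) will be reported as a proportion of all AEs";
- a participant-level proportion: "Number of participants experiencing at least one severe CTCAE will be reported as a proportion of all participants";
- a separate tabulation of surgical harms: "Surgical complication/failure and re-intervention will be tabulated and will not subject to statistical testing". A report of technical failures follows.

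The section on safety outcomes defines what is to be summarised more widely: "Safety outcomes will be measured by the number and characteristics of any AEs, and surgical complication/failure and re-intervention within 12 months". The number of AEs is also listed among the clinical-effectiveness objectives.

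The Background names harms for both treatments without grading any of them. For surgery it says "Potential complications of septoplasty include septal perforation, septal adhesions and bleeding" and "Post-operative pain is common although this is reduced if sutures rather than nasal packing are used". For the steroid sprays it says "side effects of nasal dryness, irritation and bleeding may impact on treatment satisfaction and compliance".

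The AE sentences do not say whether the summaries are split by arm. They also do not say whether the tabulation by grade counts events or participants.

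**The concern.** The event-level ratio divides one post-randomisation outcome by another. An operation and a daily spray have different profiles of minor events, so the denominator need not be comparable between arms. An arm can obtain a lower severe share simply by producing more minor events, with no participant any safer. The figure would stand in the results beside the participant-level proportion of severe events, and the two could point in opposite directions.

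There is also a mismatch of scope. The safety outcome is any AE, but the one participant-level AE proportion that the article states is limited to grade 3–5. A trial meant to inform the choice between surgery and sprays needs the chance that a patient has an event, and the article states that chance for severe events only.

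**Working it through.** The documents give no AE rate or count, so there is no safety figure to reproduce. The check is algebra plus illustrations on assumed counts.

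**Inputs.** The recruitment target is 378 (Sample size calculations) with 1:1 allocation (Randomisation), so 378/2 = 189 per arm. Every AE count below is an assumption, with one severe AE per affected participant.

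**Formulas.** For an arm with s severe AEs, m minor AEs and n participants:

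- severe share of AEs = s/(s + m);
- participant risk of a severe AE = s/n.

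The share falls as m rises; the risk does not contain m. Comparing two arms, the share is lower in the arm with the larger m/s, that is, more minor events per severe event.

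**Main illustration.**

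| Arm | Severe | All AEs | Severe share | Participant risk |
|---|---|---|---|---|
| Surgery | 9 | 180 | 9/180 = 5.0% | 9/189 = 4.8% |
| Medical | 6 | 60 | 6/60 = 10.0% | 6/189 = 3.2% |

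The share makes the medical arm look twice as severe, while the participant risk is higher in the surgical arm. Here m/s is 171/9 = 19 against 54/6 = 9.

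**How unequal the minor events must be.** Hold the severe counts at 9 and 6 and the medical arm at 54 minor AEs. The surgical share falls below 10.0% once all surgical AEs exceed 9/0.10 = 90, so once minor AEs exceed 90 − 9 = 81. That is 81/54 = 1.5 times the medical arm's minor count. Below that ratio the order does not reverse.

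**Equal severe risk.** Take 10 severe AEs in each arm, so the risk is 10/189 = 5.3% in both. With 190 minor AEs under surgery and 40 under medical management, the shares are 10/200 = 5.0% and 10/50 = 20.0%. Moving the surgical minor count from 90 to 290 moves its share from 10/100 = 10.0% to 10/300 = 3.3%, and the risk stays at 5.3%.

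**Doubled severe risk.** Take 12 severe and 188 minor AEs under surgery, and 6 severe and 44 minor under medical management. The shares are 12/200 = 6.0% and 6/50 = 12.0%; the participant risks are 12/189 = 6.3% and 6/189 = 3.2%.

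The labels can be exchanged. If the sprays produced more minor events, the distortion would favour the medical arm.

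**The case against.** The strongest reply is that the safeguard is the very next sentence. The participant risks in the illustrations are exactly what it asks for, so the reversed order would mislead only a reader who ignored the adjacent figure. This stands, and it limits the weight of the point. A reader might infer that severe risk is hidden; it is not.

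A second reply is that the ratio is not written as a comparison of arms. The same section specifies presentation by arm and overall for the subjective scales, and the section on exploratory outcomes does so for the airflow measures, but the AE sentences do not. This also stands. A split by arm is the natural reading in a two-arm trial but it is not stated, so the conclusion is conditional on that reading.

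Two stronger readings are tempting and should not be drawn:

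- *The participant-level summary misses most of the named harms.* The Background gives no grades, and any named harm of grade 3 or above would be counted. AEs of all grades are tabulated, and surgical complications, failure and re-intervention have their own table. Nor can one say that these harms appear only as event counts, because the unit of the tabulation is not stated.
- *The surgical arm will accumulate more minor events.* No figure supports this. Under Safety reporting, each arm has a call two weeks after its own starting point (randomisation or surgery). The operation is specified as sutured without packing, which the Background links to less pain. The sprays are used for six months and have minor side effects of their own.

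Finally, any-grade percentages, rows for each named harm and intervals for risk differences are details that a condensed article may leave to the full protocol or analysis plan. Their absence would not be a finding by itself. What that reply does not answer is the ratio, which the article affirmatively chooses.

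**Conclusion.** The point holds in a limited form. The severe share of all AEs is a poorly chosen summary: it does not measure risk, it moves with the number of minor events, and if read by arm it can equalise, exaggerate or reverse a real difference. In the main illustration it shows 5.0% against 10.0% where participant risks are 4.8% and 3.2%. Those percentages rest on assumed counts, one severe event per affected participant and 189 per arm. Only the mechanism is certain; neither its direction nor its size in this trial can be known from the documents.

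The accompanying participant-level proportion is sound but narrower than the article's own definition of the safety outcome. The consequence is confined to safety reporting. The primary analysis and the sample size are unaffected, and the importance is minor.

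**What to change.** Delete the sentence on severe events as a proportion of all AEs, or keep the figure only as a description pooled over arms and say that it is not for comparing them. In its place, state that the following will be reported by arm: the number and percentage of participants with at least one AE of any grade, the already planned number and percentage with at least one grade 3–5 AE, and total event counts beside them.

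Rows for each named harm and risk differences with 95% confidence intervals would be useful but optional, and the fix does not depend on them.

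The cost is a change of wording and one table. AEs are already recorded for each participant at the visits and safety calls and are to be graded for the planned tabulation, so no new data are needed.

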##### Analysis of exploratory outcomes

Three measurements each of PNIF and NPR during maximal inhalation will be made. Either the maximum (PNIF) or average (NPR) value is used.

Summary statistics will be presented for PNIF and NPR by arm and overall, at baseline, 6-month and 12-month follow-ups.

#### Mixed-method process evaluation

##### Design

The process evaluation incorporates the QRI and mixed qualitative methods. Data collection and analysis will commence during study set-up and continue throughout the trial.

Randomising patients between surgical and medical arms can be challenging. The QRI, based at Bristol University, will assist in the identification and methods of addressing such challenges. The QRI uses novel qualitative and mixed-method approaches pioneered during the National Institute for Health Research (NIHR) Health Technology Assessment (HTA)-funded ProtecT (Prostate testing for cancer and Treatment) study [42]. These methods have since been applied to several other ‘challenging’ or controversial RCTs in different clinical contexts, all of which have led to insights about recruitment issues and the development of generic and bespoke strategies to optimise recruitment [43].

The QRI will coincide with the study set-up and the first year of recruitment, using qualitative and novel methods to investigate and address recruitment barriers (objective A, below) [43–45]. Qualitative interviews will be conducted throughout the trial to investigate patients’ and clinicians’ experiences of the study procedures, interventions and barriers to implementing findings into practice (objectives B and C, below).

##### Sampling strategy

The sampling strategy is informed by current and prior experience [42, 46, 47]. In keeping with the principles of rigorous qualitative research, sampling will be responsive to the study context. In some cases fewer interviews or observations will be conducted, and in others, additional data will be required to accommodate our emerging analysis or study events. Numbers of interviews will be guided by ‘data saturation’ – continued sampling until findings become repetitious.

##### Objective A: Optimising recruitment – QRI (study set-up and first year of recruitment)

Working in close collaboration with the Trial Management Group (TMG), the QRI team will assimilate investigational and interventional approaches to understand and address recruitment difficulties in the early stages of NAIROS. The findings and implications of the QRI will continue to be implemented by the TMG and study investigators throughout the remainder of the trial recruitment period. The QRI will proceed in two iterative phases: a detailed understanding of the recruitment process will be developed in phase I, leading to tailored interventions to improve recruitment in phase II.

Phase I: understanding the recruitment process and how it operates in individual centres. A multi-faceted, flexible approach will be adopted, comprising one or more of the following methods:
In-depth interviews, conducted with: members of the TMG (*n* = 5–10); clinicians or researchers involved in trial recruitment (*n* = 10–12); and eligible patients who have been approached to participate in the trial (*n* = 5–10). Interviews will explore views on trial processes, perceptions of equipoise, and information about how the protocol is operationalised in clinical centresAudio-recording and non-participant observation of consultations during which the trial is discussed with patients, enabling identification of clear and subtle obstacles to recruitmentMapping of eligibility and recruitment pathways – noting the point at which patients receive information about the trial, which members of the clinical team they meet, and the timing and frequency of appointments. The QRI researcher will work closely with the clinical trials unit to compose logs of potential RCT participants as they proceed through screening and eligibility phasesRegular observation of TMG and investigator meetings to gain an overview of trial conduct and overarching challenges (logistical issues, etc.)Scrutiny of study documentation (e.g. PISs) to identify aspects that are unclear or potentially open to misinterpretation

Phase 2: development and implementation of recruitment strategies. Anonymised findings from Phase I will be presented to the TMG, summarising the factors that appear to be hindering recruitment. A plan of action will be devised in collaboration with the TMG if there is consensus that aspects of practice are amenable to change. Interventions will be tailored to the nature of recruitment challenges identified. Generic forms of intervention may include ‘tips’ documents on how to explain trial design and processes. Supportive feedback will be a core component of the plan of action, with the exact nature and timing of feedback dependent on the issues that arise. Centre-specific feedback may cover institutional barriers, whilst multicentre group feedback sessions may address widespread challenges. Individual confidential feedback will be offered where there is a need to discuss specific challenges or potentially sensitive issues.

##### Objectives B and C: understanding experiences of septoplasty and non-surgical management

We will investigate patients’ (*n* = 16–20) and health professionals’ (*n* = 16–20) experiences of the interventions and trial participation through qualitative interviews conducted during patient follow-up. Where possible, patients for the follow-up interviews will include those interviewed during the recruitment phase; additional participants will be recruited based on purposive and emergent criteria (e.g. patients who have declined their allocated treatment). We will identify any aspects of the care pathway which are problematic for patients or health professionals; and potential barriers and facilitators to wider acceptance and implementation of trial findings. A focus group of GPs will explore preliminary trial findings and discuss implications for primary care management of nasal obstruction. Our analysis of the implementation of study findings will be informed by Normalisation Process Theory (NPT) [48].

##### Qualitative data management and analysis

All interviews will be audio-recorded, transcribed verbatim and edited to ensure anonymity of respondents. Contemporaneous field notes from non-participant observation in clinical settings will be edited to ensure anonymity of participants. Data will be managed using NVivo software. The analysis will be conducted according to the standard procedures of rigorous qualitative analysis which we have described previously [49], including open and focussed coding, constant comparison [50], memoing [50], deviant case analysis [51] and mapping [52]. We will undertake independent coding and cross-checking and a proportion of data will be analysed collectively in ‘data clinics’ where the research team share and exchange interpretations of key issues emerging from the data. Audio-recorded recruitment consultations will be subjected to content, thematic and novel analytical approaches, including targeted conversation analysis [52] and quanti-qual appointment timing (the ‘Q-Qat method’) [53]. There will be a focus on aspects of information provision that is unclear, disrupted, or potentially detrimental to recruitment and informed consent.

#### Post-trial care

All participants who complete the NAIROS trial, or who discontinue the treatment interventions at any point, will be offered standard, local NHS care in discussion with their local investigator.

#### Indemnity

The sponsor will provide indemnity in the event that trial participants suffer negligent harm due to the management of the trial. This indemnity will be provided under the NHS indemnity arrangements for clinical negligence claims in the NHS.

#### Access to the final trial dataset

The Trial Steering Committee (TSC), Data Monitoring Committee (DMC), trial statistician, data manager and other members of the central trial team as required will have access to the full trial dataset. Individual site trial datasets will not be available to individual site investigators prior to publication of the main trial results. All requests for data should be directed to the corresponding author for consideration. Access to the anonymised final trial dataset may be available following review; we will retain exclusive use until publication of major outputs.

#### Dissemination of trial results

The results of the trial will be presented at topic-specific national or international conferences and published in a general medical journal with the monograph published by HTA. Authorship of all publications will be on a named individual authorship basis. For each publication, all individuals who fulfil the authorship definition for the publishing journal or site will be included as individually named authors. Authorship order will be decided by the chief investigator and TMG.

A lay summary of results and the HTA report will be available on the NAIROS website. Members of the Patient and Public Involvement (PPI) panel will review results and they will be involved in writing lay summaries of results for dissemination to relevant patient groups.

#### Trial monitoring

NCTU staff will monitor trial conduct and data integrity to ensure that the trial is conducted in accordance to the latest directive on GCP (2005/28/EC). This will be detailed in a Data Management Plan and a Monitoring Plan approved by the trial sponsor.

##### Safety reporting

Delegated nursing staff will interview participants to collect and record any AEs. This will take place at every trial visit (*n* = 3), and also via safety phone calls; 2 weeks after randomisation for medical management arm participants, and 2 weeks after septoplasty for surgical arm participants.

Serious adverse events (SAEs) will be assessed for any relationship to the treatment intervention (causality), and expectedness (by reference to the Reference Safety Information (RSI)) of any serious adverse reactions (SARs). Only a qualified medical doctor, delegated to do so at site, may assess the causality and expectedness of each SAE.

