#### Intervention – medical management

Patients randomised to the medical management arm will be asked to use a combination of an isotonic spray with a full twice-daily dose of a fluorinated steroid spray (mometasone furoate) which is a typical maximal medical therapy regime over a 6-month period. Preparatory work by the chief investigator indicated that most patients referred from their GP have never used this sustained combination therapy.

Sterimar Isotonic Nasal Spray dose: one spray (metred dose) into each nostril prior to using the Mometasone Nasal Spray.

Mometasone Nasal Spray dose: 100 mcg (two sprays) into each nostril twice daily for 6 weeks, followed by 100 mcg (two sprays) into each nostril once daily or 50 mcg (one spray) into each nostril twice daily for the remainder of the 6-month period.

Participants who wish to discontinue their allocated treatment, but remain in the trial, may access other treatments via the standard local NHS route. Such participants will be followed up as per their allocated treatment intervention arm. Participants in the surgical arm who wish to pursue medical treatment will not receive the trial Investigational Medicinal Product (IMP) prescription. Participants in the medical arm who wish to receive surgery and remain eligible for septoplasty should be added to the elective NHS waiting list.

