##### Surgical arm data

The operating surgeon will record:
Date of surgeryTime into and out of theatre and duration of anaestheticHighest grade of anaesthetist and surgeonWhether septoplasty ± unilateral turbinate reduction was carried outTechnical aspects of the surgical procedure (flap type, closure, use of mattress sutures to septum, use of packs/splints)Whether there were any complicationsDischarge medication (concomitant medication)

Site nursing staff will record details of any concomitant medication and AEs during a phone call at 2 weeks after surgery has taken place, and at all scheduled trial visits.

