##### Medical management arm data

As a pragmatic trial using standard treatment as part of the medical management arm, precise assessment of any mometasone furoate spray and Sterimar spray residuum will not take place. Participant compliance with the IMP does not form part of the trial monitoring plan. Participants will be asked at the 6-month follow-up visit (visit 2) to estimate how many bottles of the Sterimar and mometasone furoate spray they used.

Site nursing staff will record details of concomitant medication and any AEs during a phone call at 2 weeks post randomisation and at all scheduled trial visits.

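### The post-operative safety call follows allocated arm, so a septoplasty in a medical-arm participant gets no safety call timed to the operation

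*Protocol article*

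**What the plan says.** All references are to the protocol article.

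- **Safety reporting.** Adverse events are collected by interview: "This will take place at every trial visit (*n* = 3), and also via safety phone calls". The timing of the call depends on the arm: "2 weeks after randomisation for medical management arm participants, and 2 weeks after septoplasty for surgical arm participants".
- **Surgical arm data.** Nursing staff ask about adverse events and concomitant medication "during a phone call at 2 weeks after surgery has taken place, and at all scheduled trial visits". The same section holds the only specification of an operative record. It opens "The operating surgeon will record" and lists, among other items, the procedure done, complications and discharge medication.
- **Medical management arm data.** Here the contact is "during a phone call at 2 weeks post randomisation and at all scheduled trial visits". No operative record and no post-operative contact appear in this section.
- **Intervention – medical management.** On participants who stop their allocated treatment but remain in the trial: "Such participants will be followed up as per their allocated treatment intervention arm". Crossover to surgery is foreseen: "Participants in the medical arm who wish to receive surgery and remain eligible for septoplasty should be added to the elective NHS waiting list".
- **Safety outcomes.** "Safety outcomes will be measured by the number and characteristics of any AEs, and surgical complication/failure and re-intervention within 12 months".

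**The concern.** The post-operative call exists to find early harm from an operation, but its trigger is written by allocation. The plan expects some participants to receive the other arm's treatment and keeps them on their allocated schedule. The two rules together leave some operations outside the scheme meant to observe them.

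At stake is the evenness of the surgical safety data. Complications and failure within 12 months are a named safety outcome. For operations in the surgical arm they would be sought from a surgeon's record, a call at two weeks and the visits. For the same operation in a medical-arm participant, only the visits are assured. Early and self-limiting complications are the ones most likely to be forgotten or misdated when first asked about months later. Any summary by treatment received would then pool operations observed with different intensity.

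**Working it through.** The point rests on reading the sections together; the arithmetic only illustrates scale.

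**1. The four possible cases, as written**

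| Allocated arm | Septoplasty during follow-up | Early safety call | Operative record | Next scheduled adverse event enquiry |
|---|---|---|---|---|
| Surgical | Yes | 2 weeks after operation | Specified | Month 6 visit |
| Surgical | No | No trigger occurs | Not applicable | Month 6 visit |
| Medical | No | 2 weeks after randomisation | Not applicable | Month 6 visit |
| Medical | Yes | 2 weeks after randomisation; none tied to the operation | Unclear: specified only under the surgical-arm heading | Month 6 or month 12 visit, whichever follows the operation |

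The second and fourth rows are the gaps. The missing post-operative call in the fourth row follows directly from Safety reporting, which limits that call to the surgical arm, and from the rule that participants who switch are followed by allocation. The uncertain operative record is a weaker inference, from the placement of the list under one arm's heading.

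**2. Delay before complications are asked about**

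The three trial visits are at baseline, 6 months and 12 months.

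- Surgical arm, operated on within the window of 8 weeks (+ 4 weeks): the call falls by week 8 + 2 = 10, or at the latest week 12 + 2 = 14. The delay after surgery is always 2 weeks.
- Medical-arm crossover operated on at month *m* after the month 6 visit: the delay is 12 − *m* months. For *m* = 7 it is 12 − 7 = 5 months. The limit, just after the month 6 visit, is close to 6 months.
- Surgical-arm participant never operated on: no scheduled adverse event contact between baseline and month 6.

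**3. How many participants could be affected**

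The recruitment target reproduces as 302 / 0.8 = 377.5, rounded up to 378. With 1:1 allocation, 378 / 2 = 189 per arm. The article states no crossover rate. Purely as an assumption, let *f* be the share of the medical arm operated on within 12 months:

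| *f* | Operations, 189 × *f* | Share of all septoplasties if all 189 surgical-arm participants are operated on, *f* / (1 + *f*) |
|---|---|---|
| 5% | 9.45, about 9 | 0.05 / 1.05 = 4.8% |
| 10% | 18.9, about 19 | 0.10 / 1.10 = 9.1% |
| 20% | 37.8, about 38 | 0.20 / 1.20 = 16.7% |
| 30% | 56.7, about 57 | 0.30 / 1.30 = 23.1% |

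The last column rises if some of the surgical arm is not operated on. With 10% crossover and 10% unoperated it is 0.10 / (0.90 + 0.10) = 10%. It falls if waiting-list operations come after month 12, since those lie outside follow-up.

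**The case against.** The best reply is that the article leaves several safeguards in place, and most of it stands.

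- Adverse events are asked about at every visit in both arms, and the assessment of serious events is not limited by arm. Economic outcomes adds the Health Care Utilisation Questionnaire at 6 and 12 months, which records the use and timing of additional interventions. A crossover operation and any re-intervention should therefore come to light. But the questionnaire is described as recording use and timing, not operative complications, and a visit may come months after the event.
- Medical-arm crossovers do receive a two-week call. It is timed from randomisation, so it will normally precede any operation obtained through a waiting list.
- A reader might infer that crossover operations go unrecorded. The article does not say so. The wording under Surgical arm data is tied to the operation and the operating surgeon, and the allocated-arm rule can be read as ordinary intention-to-treat retention. Only lack of clarity can be claimed.
- A reader might also infer a biased between-arm test of harms, with surgical complications charged to medical management. Analysis of secondary outcomes plans descriptive tabulation, with no statistical testing of surgical complications, failure or re-intervention. It does not fix whether that tabulation is by allocation or by treatment received. That stronger reading is not supported.
- An unoperated surgical-arm participant has had neither the trial operation nor the trial spray, so little harm from trial treatment could be missed early. This is why that case is secondary.
- The full protocol may deal with crossovers; the table of key changes says version 5.0 clarified options for people leaving their allocated treatment. That is possible but cannot be checked, and it does not alter an arm-based trigger that the article gives in three sections without exception.

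**Conclusion.** The concern holds in limited form. As written, medical-arm participants who have septoplasty during follow-up get no safety call timed to the operation, and the article leaves open whether an operative record is completed for them. Surgical-arm participants who are never operated on have no scheduled adverse event contact before month 6, a lesser matter.

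The consequence is uneven early ascertainment for the outcome of surgical complication or failure within 12 months, and for any safety summary by treatment received. The section on analysis of the primary outcome allows an as-treated approach to non-compliance, so such a summary is plausible, though the article does not commit to one. It is not a general loss of safety data and does not touch the primary comparison of SNOT-22.

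The size cannot be stated. The range of 9 to 57 operations rests wholly on an assumed crossover of 5% to 30% and on those operations falling within 12 months. The gap itself exists at any crossover rate above zero.

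**What to change.** These changes concern data collection and reporting only; efficacy follow-up stays by allocation.

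1. In Safety reporting, attach the two-week post-operative data-collection call to any septoplasty during follow-up, whatever the allocation.
2. In Surgical arm data, state that the operative record covers any such operation, completed from the hospital notes where the surgeon is outside the trial team.
3. Reconcile Intervention – medical management, Surgical arm data, Medical management arm data and Safety reporting, so that they say what early adverse event contact a surgical-arm participant has when no operation takes place.
4. Tabulate surgical complications by operation received as well as by allocated arm.

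The cost is one extra call and one existing form per crossover, plus one further descriptive table. The drawback is that records completed from notes may be less full than those written by a trial surgeon, so the source should be flagged in the data.
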